## Methods/Design

A two-group randomized controlled trial design with pretest and posttest measures will be used to address the study aims. Distressed breast cancer survivors will be randomized equally to one of two groups: (a) P-OSG, a facilitated OSG with structured helping opportunities and coaching on how to recognize and be responsive to others needs for help or (b) S-OSG, a comparison standard facilitated OSG. Data will be collected approximately one month before and after the intervention. The study design is guided by the CONSORT criteria [52]. The study is in compliance with the Helsinki Declaration and has received approval from the Temple University Institutional Review Board (protocol number 13705).

### Participants

Eligibility inclusion criteria are: diagnosed with stage I or II breast cancer within the preceding 36 months; age 21 to 65 years (the age cap minimizes sampling women with cognitive or physical impairments that could limit participation and maximizes sampling women with computer experience), access to and ability to use a computer and the Internet, able to understand the informed consent form, fluent in spoken English, and meet the screening criteria for psychological distress. Women will qualify as distressed if they fall above the "non-case" cut-point (≥ 8) on either the depression or anxiety subscale of the Hospital Anxiety and Depression Scales (HADS [53]). This approach will generate a sample with a range of subclinical and clinical levels of distress symptoms [54]. We will not exclude women who previously have participated in an OSG or received other psychosocial treatments. Instead we will measure these variables and include them as covariates in analyses if necessary.

### Measures

All major study measures have established reliability and validity. The primary outcome measure will be the HADS, which has been used extensively and validated with breast cancer and other cancer patient populations [57]. The HADS can be used to generate continuous measures of symptoms of depression and anxiety and also provides clinical cut-offs. The secondary outcome, sense of purpose, will be measured using the validated and reliable Meaning in Life Questionnaire [58]. Validated and reliable measures also will be used to assess the three mediators: self-esteem with Rosenberg's Self-Esteem scale [59], positive affect with the Positive Affect Scale [60], and sense of belonging (i.e., mattering to others) with the General Mattering Scale [61].

Measures of potential covariates include background variables (e.g., age, race, treatments) and other potential confounding variables [e.g., Social Provisions Scale [62] to measure social support received by social network members, Comorbidity Questionnaire [63] to measure comorbid health conditions, and questions about receipt of formal (e.g., counseling, medication) and informal (e.g., support groups) psychosocial interventions including participation in online support groups unrelated to the study]. Level of "satisfaction" with and perceived "helpfulness" of different intervention elements (e.g., support received, opportunities to help others, interactions with facilitators) will be assessed using 5-point Likert-type scales (1 = very unsatisfied to 5 = very satisfied).

Finally, as a manipulation check, we will assess if the P-OSG intervention increased helping behaviors relative to the S-OSG. Research assistants will code instances of online support provisions using Bambina's Support OnLine (SOL) coding scheme [64]. SOL can be used to reliably code major categories of informational and emotional support provision. Coders will be blind to intervention condition. As part of the process assessment, P-OSG participants also will answer questions about perceived barriers or concerns with the "outreach" and "blogging" activities (see below).

### Interventions

#### Standard online support group intervention

The S-OSG comparison condition is based on an empirically validated facilitated breast cancer OSG [3,29]. The intervention is manualized and interventionists will receive regular monitoring and supervision by PhD-level clinical psychologists with experience running cancer OSGs. The OSGs are modeled after face-to-face support groups [e.g., [65,66], such as those conducted in community settings throughout North America (i.e., Gilda's Club, Cancer Support Community). While the proposed OSG is distinct in that specific topics are introduced at each session, several components remain consistent with the face-to-face model; including all sessions are professionally led and participants are considered the experts in their own experience. The groups will meet online weekly for approximately 1.5 hours and participants will be able to email and chat. Each week the facilitator will introduce a new topic and encourage participants to share their relevant experiences, concerns, and problems. The facilitator will not encourage people to help others, but instead focus on promoting self-expression (e.g., "Tell us more about the pain in your arm.").

The weekly topics, which were drawn from research on breast cancer survivorship [e.g., [67-69], include: (1) symptoms of pain, fatigue and lymphedema; (2) self-esteem and body image concerns; (3) problems in physical and recreational activities; (4) problems in intimacy, sexual interest and function; (5) coping with depression, anxiety, and fears of recurrence; and (6) challenges to staying healthy (diet, exercise, surveillance). In addition, as a control for the "helping blog" activity in the P-OSG condition (see below), participants in the S-OSG will be asked to select one of the six weekly topics that they wish to write about as a way to organize some of their thoughts and feelings. This type of writing is similar to expressive writing, which no study to date has found to be effective in reducing psychological distress in breast cancer survivors [70], so it serves as an effective attention control for the "helping blog" activity. The writing will be private and not shared with anyone, including the research team.

#### Prosocial online support group intervention

The P-OSG intervention includes elements of the S-OSG, but with critical modifications and key additions. First, participants will receive a tip sheet that describes how to recognize others' needs for different kinds of support and how to be helpful in an online environment. Second, the facilitator will post reminders at the beginning of each session on the importance of responding to one another's needs for help. Third, participants will be asked to commit to a goal of offering informational or emotional support to group members each week during the live synchronous sessions or later using the discussion board, email or chat. Fourth, prior to each week's meeting, participants will receive an email describing the topical problem to be discussed (e.g., pain, fatigue, and lymphedema). Their "homework" is to prepare 1-2 sentences on how their experiences with the problem might help others to cope with the problem. If they have not had the problem, they will be asked to write 1-2 sentences on how their approach to coping with other life problems might be useful to group members coping with the particular problem of the week. Fifth, the facilitator will encourage helping by highlighting direct and indirect requests for support by group members, will praise those who offer help (e.g., "Nice suggestion, Margie."), and will encourage additional help (e.g., "Has anyone else found a good way to cope with the problem Joan mentioned?").

Members of the P-OSG also will be asked to select one of the six weekly topics to prepare a blog about the topic to share with the group. The goal will be to write about their experience as a way of helping other breast cancer survivors who have gone through a similar experience. The writing instructions will emphasize that participants should not worry about grammar or spelling and that if they wish the research staff can help to edit their writing for grammar or spelling before posting. Participants will be asked to blog about any effective ways they have developed to cope with a cancer-related problem. The exercise will emphasize that people often have experiential knowledge that is valuable to others, but can only be accessed if there is sharing. Bloggers will be told that the exercise is designed to help other patients to understand the different consequences of breast cancer and its treatment, as well as how they might best manage or address these consequences. Instructions also will explain that the bloggers do not necessarily have to provide answers or solutions to the problems they write about, they simply need to share their experience. Reading others similar experiences can help to normalize the experience or make readers feel less alone. We recognize that some participants might be resistant to sharing their writings with others, either because they do not feel it will be valuable or they feel it is too personal. We will offer individuals the opportunity to have their blog posted anonymously, or only post select information, or for us to paraphrase what they have written in a list of comments comprised of input from multiple blogs. All blogs will be fact checked by research staff to avoid posting misinformation.

Finally, in addition to promoting helping within the group, the P-OSG will promote helping outside of the group through an outreach activity called the "Breast Cancer Awareness Ambassadors" program. Women in the P-OSG group will be asked to increase breast cancer awareness by sharing a "Breast Cancer and You" fact sheet and "Mammograms Save Lives" e-Cards, both developed by the Centers for Disease Control and Prevention, with women in their social network who are 40+ years old.

### Analytic Plan

Descriptive statistics will be generated for the total sample and the treatment groups for each time point. Distributional properties will be analyzed to determine if variance stabilizing or normalizing transformations should be applied. Outliers will be assessed and checked for accuracy. Non-response and attrition must be addressed in longitudinal research [71]. Therefore, full information maximum likelihood (FIML) and multiple imputations (MI) will be used to correct for missing data [71]. Variables associated with missing data mechanisms will be included as covariates in models or used to create multiple imputations as appropriate. Both FIML and MI are implemented in a variety of software packages including LISREL, AMOS, and MPlus, each of which can accommodate all statistical models (ANCOVA, OLS and logistic regression, mediation models, etc.) that will be estimated in this project.

Hypotheses 1 and 2: Post-test differences between P-OSG and S-OSG in primary and secondary outcomes will be tested using ANCOVA, with intervention group as the predictor and appropriate pre-test scores as covariates. Intent-to-treat analyses will be used. Variance associated with cohort membership will be estimated via intraclass correlation coefficients. If necessary cohort can be entered into the ANCOVA models as a random effect or fixed-effects analyses can be performed if there is evidence for unobserved heterogeneity. Group-level analyses can be performed on aggregate data if necessary.

Hypotheses 3 and 4: Mediation will be tested in a series of ANCOVA models using standard statistical software or structural equation modeling software. Hypothesis tests will be based on bootstrapped standard errors [72].

Hypothesis 5: Acceptability will be assessed by recruitment and retention rates, reasons for refusal/dropout, and level of participants' ratings of satisfaction and helpfulness of different intervention elements. Fisher's exact test will be used to evaluate differences between conditions for categorical outcomes; t-tests or non-parametric equivalents can be performed to compare ordinal or continuous outcomes.

The feasibility of manipulating online helping behavior will be assessed by comparing mean levels of observed helping behaviors (using SOL data) enacted by participants in the P-OSG versus S-OSG and participants' willingness and ability to generate a "helping blog" and engage in "outreach" activities in the P-OSG condition. Additional analyses will be conducted to confirm that treatment fidelity was equivalent across conditions and to explore dose-response relations by examining whether level of participation (e.g., attendance, number of posts, amount of help provided to others) moderates intervention effects.

Because this is a preliminary study of the effect of the novel P-OSG intervention, we are interested in estimating effect sizes of the P-OSG intervention group. More specifically, we are interested in gaining an estimate of the true treatment effect size (which is independent of sample size) and to establish a plausible confidence interval around this effect size. Thus, we present information regarding the aim of accuracy in parameter estimation (AIPE) [73] as well as information relevant to the aim of null hypothesis significance testing.

AIPE identifies a range (half-width, *w*) within which an effect size can be bracketed with a specified probability, independent of the magnitude of the observed effect size. It is easiest to interpret in the metric of standardized regression coefficients, i.e., β ± *w*. For these analyses, AIPE will depend on (a) the number of predictors, (b) variance in predictor of interest accounted for by other predictors, $R_{xx}^{2}$, and (c) overall variance predicted in outcome, $R_{yx}^{2}$. Our models will have between 2 (pre-test & treatment) and 10 predictors (i.e., adding 3 mediators and possibly 5 cohort identifier dummy variables). We estimated half-widths assuming: model $R_{yx}^{2}$ was either high (.5) or low (.1) and $R_{xx}^{2}$ was zero (treatment), low (.1) or high (.5). With 80% probability for N = 180 (90 per experimental condition), we expect to be able to bracket effect sizes for treatment effects within ± .11 to ± .15 depending on model R^2^. Effect sizes for mediators will be estimated with somewhat less precision but within ± .12 to ± .22

Power to identify post-test differences between P-OSG and S-OSG controlling for pre-test values and group membership depends on the correlation between pre-test and post-test scores. Minimum detectable effect size $\left(\hat{d}\right)$ with power = .8 and α = .05, is well approximated (R^2 ^> .99) for specific pre-post correlations (r_01_) by the formula: $\hat{d}=0.41+0.08r_{01}-0.36r_{01}^{2}$ and ranges from .19 (r_01 _= .9) to .42 (r_01 _= 0).

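### The default H1/H2 analysis ignores clustering by online group, and the optional cohort term would probably not capture it, so the treatment standard error is too small whenever the group ICC is above zero

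*Protocol article*

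**What the plan says.** Allocation is individual: "Distressed breast cancer survivors will be randomized equally to one of two groups" (Methods/Design). Treatment is delivered in facilitated groups: "The groups will meet online weekly for approximately 1.5 hours and participants will be able to email and chat" (Standard online support group intervention). The prosocial arm asks members to commit to supporting one another every week.

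For H1 and H2 the Analytic Plan names ANCOVA with condition as predictor and the pre-test score as covariate. Variance due to cohort membership is to be estimated by intraclass correlation. Then: "If necessary cohort can be entered into the ANCOVA models as a random effect or fixed-effects analyses can be performed". The next sentence also permits group-level analysis of aggregate data, again only if necessary. No criterion is given for either step, and neither cohort nor group is defined.

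The precision paragraph counts up to 10 predictors, starting from pre-test and treatment and "adding 3 mediators and possibly 5 cohort identifier dummy variables". It takes the share of treatment variance explained by the other predictors as zero, for "N = 180 (90 per experimental condition)". The power paragraph gives a minimum detectable effect "with power = .8 and α = .05" that "ranges from .19 (r_01 _= .9) to .42 (r_01 _= 0)", described as "controlling for pre-test values and group membership". It states no ICC, group size or design effect.

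**The concern.** Members of one online group share a facilitator, a weekly conversation and, in the prosocial arm, a deliberate exchange of help. Some correlation of post-test scores within a group is what the intervention sets out to create. The treatment contrast is made between groups, so variance between groups belongs in its standard error.

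The default model has no term for it. The optional cohort term does not supply one if each cohort contains groups from both arms: it removes only what those groups have in common. The result would be intervals that are too narrow and too many false positives on the primary outcome (H1) and on H2. The article says its aim is a plausible confidence interval for the effect size, so this bears directly on the trial's stated product. The comparison of coded helping behavior has the same problem, because posts in one chat answer each other.

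**Working it through.** **Inputs from the article.** 180 women, 90 per arm; power .80; α .05 (sidedness not stated; two-sided reproduces the figure); 5 cohort dummies, hence 6 cohorts.

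**Inputs assumed.** Residual group ICC ρ of .01, .02, .05 and .10. Either one group per arm per cohort (12 groups of 15) or two (24 groups of 7–8).

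**Step 1: the plan's own figure.** With independent observations, d = (1.960 + 0.842) × √[(2/90)(1 − r²)].
- r = 0: 2.802 × 0.149 = 0.418 (0.420 by noncentral t). Stated: .42.
- r = .9: 0.418 × √0.19 = 0.182. Stated: .19, which is the article's own quadratic: 0.41 + 0.072 − 0.292 = 0.190.

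The .42 therefore carries a design effect of 1. The half-widths for treatment (± .11 to ± .15) also reproduce with independent observations: .109 to .150 for a 95% interval with 80% assurance and 2 to 10 predictors.

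**Step 2: what cohort means.** Pre-test and treatment (2), mediators (3) and cohort dummies (5) make the 10 predictors, so treatment and the cohort dummies sit in one model. Treatment is given zero overlap with the other predictors. That fits cohorts containing both arms. If cohort were the online group nested in arm, the dummies would determine treatment completely and the overlap would be 1.

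**Step 3: variance of the treatment contrast.** With 12 groups (6 per arm) and residual variance 1:

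2[ρ/6 + (1 − ρ)/90] = (2/90)(1 + 14ρ).

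The cohort effect cancels from the contrast; the group effect does not. ANCOVA with or without cohort dummies uses roughly 2/90, so the correct standard error is larger by about √(1 + 14ρ). At ρ = .05 the design effect is 1.70, the ratio is 1.30, and the approximate true error rate is 2[1 − Φ(1.97/1.30)] = .13.

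**Step 4: results.** Error rates are simulated, with a true effect of zero and 5 cohort dummies in the model. Detectable effect and power use the noncentral t with 12 − 2 = 10 df.

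| Assumed group ICC | .01 | .02 | .05 | .10 |
|---|---|---|---|---|
| Design effect, 12 groups of 15 | 1.14 | 1.28 | 1.70 | 2.40 |
| Type I error, 12 groups of 15 | 7% | 8% | 14% | 21% |
| Type I error, 24 groups of 7–8 | 6% | 6–7% | 9% | 13% |
| Detectable effect at r = 0, 12 groups | .50 | .53 | .60 | .72 |
| Power at d = .42, 12 groups | .66 | .61 | .50 | .38 |

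With 12 groups, plain ANCOVA without cohort gives nearly the same error rates (about 13% and 20% at ICC .05 and .10), so the cohort dummies give no protection. A cohort random intercept alone leaves the same variance unmodelled. Analysis of group means held 5% at ICC .02, .05 and .10. At ICC .05 the design effect alone widens the half-widths to .109 × 1.30 = .14 and .150 × 1.30 = .20.

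**Step 5: the other reading.** If cohort meant the online group, group dummies plus treatment would be collinear. With 12 groups, the intercept, treatment, pre-test and 11 dummies make 14 columns of rank 13; with 6 groups, 8 columns of rank 7. Fixed effects could then not estimate treatment. A random effect for cohort, with suitable df, would be valid.

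**The case against.** The plan recognizes clustering and lists remedies, and the sentence on group-level analysis names one that would hold the error rate if group means the online group. That stands: a reader might infer that the plan deals with clustering through a cohort term alone, and the text does not support this.

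A reader might also infer that the treatment effect is either given too small a standard error or cannot be estimated at all. That is too strong. Non-estimability affects only the fixed-effects option, under a reading of cohort that the precision paragraph speaks against; under that same reading the random-effect option is sound.

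The size of the problem rests on assumptions. No ICC, group number or group size is given, and doubling the number of groups cuts the inflation markedly. Nor does the article say that the need for adjustment would be judged by a significance test, so nothing here depends on the power of such a test.

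Finally, this is a condensed article on a preliminary study, and a trigger rule or df method may be in a fuller plan. Their absence is not the point. The article itself states a default model without a group term, names a cohort term that would not repair it, and reports power and precision that assume independence. Being preliminary does not help, because the declared goal is an accurate interval.

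**Conclusion.** The concern holds in this form. The stated default for H1 and H2, and the cohort-term remedy on the reading the article best supports, give a standard error that is too small whenever the online-group ICC is above zero. The only listed remedies that would work are the group-level analysis, if group means online group, and a random effect, if cohort means online group; both are optional.

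The direction follows from the design. The size does not: type I error of about 7% to 21% with 12 groups of 15, or 6% to 13% with 24 smaller groups, across assumed ICCs of .01 to .10. The detectable effect of .42 is a best case that needs an ICC of zero; with 12 groups and 10 df it is about .50 to .72. The documents do not support a claim that the error rate is inflated by any particular amount, or that every listed option is invalid.

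**What to change.** - Define cohort and online group, and state the planned number and size of groups.
- For H1, H2 and the other continuous comparisons, include a random intercept for online group (cohort × condition) whatever the estimated ICC, with Kenward-Roger or Satterthwaite df. Alternatively, make the group-level analysis already named in the Analytic Plan the primary one. Delete the if-necessary condition.
- Cohort may be added on top. With one group per arm per cohort, a group-level comparison paired within cohort has 5 df, against 10 unpaired.
- Those df corrections belong to linear mixed models. For retention (planned as Fisher's exact test) and the coded helping counts, use a method that suits the outcome and allows for online group, for example a comparison of group-level summaries.
- Restate the half-widths and the minimum detectable effects over an ICC range, with the assumed number of groups.

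The cost is analysis work and wording, to be settled before unblinded data are analysed. Intervals will be wider, and stated power and precision less favourable. Recruitment and treatment need not change.

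### The stated detectable effects and half-widths assume 180 independent women with complete posttests, although both arms are delivered in interacting online groups

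*Protocol article*

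**What the plan says.** All the planning figures are in the Analytic Plan.

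- **Precision.** The treatment half-widths are given as ±.11 to ±.15, introduced by "With 80% probability for N = 180 (90 per experimental condition), we expect to be able to bracket effect sizes for treatment effects within". The listed determinants are the number of predictors, the variance in the predictor explained by the other predictors (zero for treatment) and the model R² (.1 or .5). Between 2 and 10 predictors are foreseen, possibly including five cohort dummies.
- **Power.** "Power to identify post-test differences between P-OSG and S-OSG controlling for pre-test values and group membership depends on the correlation" between pretest and posttest. The minimum detectable effect, "with power = .8 and α = .05, is well approximated" by a quadratic in that correlation, and runs from .19 at r = .9 to .42 at r = 0.
- **Grouping.** The same section will estimate ICCs for cohort and allows cohort as a random or fixed effect, or analysis of aggregate data, where needed. The intervention sections describe weekly facilitated online meetings in both arms. The prosocial arm is built to make members respond to one another.
- **Attrition.** "Non-response and attrition must be addressed in longitudinal research". Maximum likelihood and multiple imputation are planned. No loss rate is given.
- **Allocation.** "Distressed breast cancer survivors will be randomized equally to one of two groups".

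**The concern.** Women are randomized individually but treated in groups that share a facilitator and influence one another. Posttest scores within a group may therefore be correlated, and that correlation adds to the variance of the treatment contrast. The plan recognizes the possibility in its analysis but leaves it out of its power and precision.

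This matters because the plan describes the study as preliminary and gives its purpose as estimating the effect size with a plausible confidence interval. The printed detectable effects and half-widths are what a reader, or the designer of a follow-on trial, would take as the information the study can deliver.

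**Working it through.** **Inputs from the protocol article:** 90 per arm, α = .05 (two-sided reproduces, one-sided does not), power .80, r from 0 to .9, R² of .5 or .1, 2 to 10 predictors.

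**Assumed, because the article gives no values:** ICC of .01, .05 or .10, taken as the correlation remaining after adjustment for pretest; one online group per arm per cohort. Five cohort dummies imply 6 cohorts, so 6 × 2 = 12 groups of 180/12 = 15. Groups of 8 serve as a sensitivity case.

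**1. Reproduce the stated detectable effects.** The standard error of d is √[(2/90)(1 − r²)]. The noncentral t on 177 df at 80% power gives:

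| r | recomputed | plan's quadratic | plan's stated range |
|---|---|---|---|
| 0 | .420 | .41 | .42 |
| .5 | .364 | .36 | – |
| .9 | .183 | .190 | .19 |

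The match is close, not exact. The printed .19 is the value of the fitted quadratic. Adding five cohort dummies (172 df) leaves .420 and .183 unchanged.

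**2. Reproduce the stated half-widths.** w = t(.975, df) × √[(1 − R²)/df] × √[χ²(.80, df)/df].
- R² = .5: 1.973 × √(.5/177) × 1.043 = .109 with 2 predictors; .112 with 10.
- R² = .1: 1.973 × √(.9/177) × 1.043 = .147 with 2 predictors; .150 with 10.

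These are the printed ±.11 and ±.15. Neither calculation contains any clustering or missing posttests.

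**3. What cohort adjustment does.** Cohort dummies remove variation that both arms of a cohort share. They leave the variation between the two online groups within a cohort, and that difference is part of the treatment contrast. Dummies for the online groups themselves are not a way out, because each group lies wholly within one arm and the dummies would absorb the treatment effect.

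**4. Add clustering.** DEFF = 1 + (m − 1) × ICC. Detectable effect at r = 0 = .420 × √DEFF. For 12 groups the between-group df are 12 − 2 = 10, so the multiplier becomes t(.975) + t(.80) = 2.228 + .879 = 3.107, applied to √[(2/90) × DEFF]. Power is for d = .42 at r = 0, without the group-df correction.

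| m | ICC | DEFF | √DEFF | detectable d | on 10 df | power |
|---|---|---|---|---|---|---|
| 15 | .01 | 1.14 | 1.068 | .45 | .49 | 75% |
| 15 | .05 | 1.70 | 1.304 | .55 | .60 | 58% |
| 15 | .10 | 2.40 | 1.549 | .65 | .72 | 44% |
| 8 | .05 | 1.35 | 1.162 | .49 | – | 67% |

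The proportional loss is the same at every r. At r = .9, .183 becomes .195 at ICC .01, close to the printed .19, and .24 at ICC .05. At ICC .05 with groups of 15 the half-widths grow 1.30-fold: .109 × 1.304 = .14 and .150 × 1.304 = .20.

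**5. Attrition, only if 180 is the number randomized.** With an assumed 20% loss and no clustering, n = 72 per arm. The detectable effect at r = 0 is .420 × √(90/72) = .47, and power at d = .42 is 71%.

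**6. The 80% wording.** An interval with 80% coverage would use t(.90) and no assurance factor: about ±.07 (R² = .5) and ±.09 (R² = .1). The printed values are 95% interval half-widths that will not be exceeded with 80% probability.

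**The case against.** The strongest reply is that the printed figures are correctly computed for the model they describe, that the plan already intends to estimate ICCs and model cohort if needed, and that the study is preliminary. The interval finally reported will depend on the model used, not on the planning figures. The size of the loss also rests on a group size and an ICC that the article does not give. At ICC .01 the loss is small, and smaller groups reduce it further. All of this stands and limits the weight of the point. It does not remove it, because the stated power and precision still leave out a dependence that the same section anticipates.

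Four stronger readings are tempting and are not supported:

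- *The arithmetic is wrong.* It is not; the fault lies in the independence assumption.
- *The trial is bound to fall short of 180 complete posttests.* The article does not say whether 180 is the number randomized or the number analyzed. If it is the number analyzed, the attrition component disappears.
- *Half-widths in standardized coefficients beside effects in d are a mistake.* Both scales are labeled. Giving the half-width in d as well would be a convenience.
- *The 80% phrase makes precision look better than it is.* A reader who took 80% as coverage would think precision worse than it is, since true 80% intervals would be narrower. The phrase needs clarifying but is no evidence of optimism.

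**Conclusion.** The concern holds in this form: the detectable effects of .19 to .42 and half-widths of ±.11 to ±.15 belong to 90 independent women per arm with complete posttests, and they are too favorable for any positive correlation within online groups. The direction is certain; the size is conditional. With 12 groups of 15, it runs from a small loss at ICC .01 (.42 to .45, power 75%) to a substantial one at ICC .10 (.65, power 44%), and more on 10 group-level df. Any effect of attrition depends on what 180 counts. The 80% wording is a secondary matter of clarity. The point deserves correction, but it does not put the design or the planned analysis in question, so it ranks below an essential change.

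**What to change.** Keep N = 180. In the Analytic Plan:

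1. State whether 180 is the number randomized or the number with posttest data.
2. State an assumed online group size and number of groups. Restate the minimum detectable effect and the treatment half-widths for ICC .01, .05 and .10, with group-based degrees of freedom.
3. If 180 is the number randomized, add the same figures for assumed attrition, for example 10% and 20%.
4. Describe the half-widths as 95% confidence interval half-widths that will not be exceeded with 80% assurance.

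The cost is recalculation and rewording. The stated figures become less favorable; no extra participants and no change of design are needed.
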